**Methods and analysis:**

The study will be conducted in two of the five countries participating in the WHO ACTION-III trial—India (Delhi, Belagavi) and Nigeria (Ibadan and Ile-Ife). We will use a population PK approach using sparse sampling to study the PK effects of the two ACS regimens, that is, 6 mg dexamethasone phosphate (DEXp) or 2 mg betamethasone phosphate (BETp), administered intramuscularly every 12 hours for a maximum of four doses or till birth, whichever is earlier, compared with placebo. We will also ascertain the fetal–maternal ratio of DEXp and BETp at birth.

Maternal venous blood samples will be collected at 0, 1–4 hours, 8–12 hours after the first dose, and at 24–36 hours, 48–60 hours, 72–96 hours after the last dose, and immediately after birth, along with cord blood. Concentrations of DEXp and BETp will be measured at set time points using a validated liquid chromatography mass spectroscopy assay. PD parameters measured will include total and differential white blood cell count (by automated analysers using electrical impedance), plasma glucose (hexokinase method) and serum cortisol (using a validated electrochemiluminescence immunoassay), at predefined time points. PK models will be developed for each drug using non-linear mixed effects methods. Optimal dosing will be investigated using Monte Carlo simulations.

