### Study procedures

Serial maternal blood samples will be collected starting before the administration of the first dose of IMP up to 96 hours after the last dose, through a dedicated indwelling cannula or by venipuncture. A cord blood sample will also be collected at birth. The sampling schedule is provided in table 1. All study sites will collect the samples at time points within the sampling time window depicted in table 1 (see online supplemental appendix table 1 for site-specific schedules). The sampling time points for the PK and PD analysis are indicated in table 1.

**Table 1 T1:** Blood sampling schedule

Sample number	Sampling time point	Maternal PK (BETp and DEXp)	Maternal PD (cortisol, glucose, WBC counts)	Cord PK+PD
1	*Baseline (−0.5 hours to 0 hours)*	√	√	
2	1–4 hours post first dose	√	√	
3	8–12 hours post first dose	√	√	
X*	At birth	√	–	√
4	24–36 hours after the last dose†	√	√	
5	48–60 hours after the last dose†		√	
6	72–96 hours after the last dose†		√	

PD parameters include serum cortisol, plasma glucose, total and differential WBC count (neutrophils, basophils and lymphocytes).

Windows for all draws ±30 min, except sample 6. Sample 6 to be drawn as close as possible to the stated time point for the site, otherwise at the point of discharge.

* Birth can happen at any time therefore, birth sample is not numbered sequentially and is labelled as X.

† Regardless of the time of birth.

BETp, betamethasone phosphate; DEXp, dexamethasone phosphate; PD, pharmacodynamics; PK, pharmacokinetics; WBC, white blood cell.

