#### Model building procedures

A base model will first be developed for the pretreatment and placebo measurements, the PK of each drug, and each PD biomarker using the models established by Krzyzanski *et al*.^28^ Once adequate base models have been developed, the joint drug/PD models and covariate effect models will be built. To ensure reasonable initial estimates, we will use the results from the Krzyzanski study.

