#### Random effect models

The between-subject variability will be estimated for all parameters where feasible. A log-normal parameter variability model or other appropriate parameter variability models will be considered for the PK and PD parameters. For the residual unidentified variability, additive, proportional and a combined additive and proportional error models will be considered.

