#### Statistical analysis

Drug-related PK and PD individual parameters (eg, V, CL, ka, Emax, EC50) will be summarised using descriptive statistics. Two-way analysis of variance will be applied to test for between drug differences. The population estimates of PK-PD parameters will be compared using 95% CIs. For the model selection, the χ^2^ test for significance of the change in the maximum likelihood objective function will be used. For the selection of significant covariates, the likelihood ratio test will be applied.

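### The two-way ANOVA for between-drug differences treats shrunken individual PK estimates as data, so it exceeds its nominal level; the model-based comparison should carry the inference

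*Protocol article*

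**What the plan says.** The Statistical analysis section of the protocol article begins: "Drug-related PK and PD individual parameters (eg, V, CL, ka, Emax, EC50) will be summarised using descriptive statistics". The next sentence is: "Two-way analysis of variance will be applied to test for between drug differences". The two factors are not named and no significance level is given. The section then adds a second comparison: "The population estimates of PK-PD parameters will be compared using 95% CIs". It uses likelihood-based tests for model selection and covariates.

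The individual values come from population models fitted drug by drug. The abstract says: "PK models will be developed for each drug using non-linear mixed effects methods". Model building procedures says: "A base model will first be developed for the pretreatment and placebo measurements, the PK of each drug, and each PD biomarker". The data are sparse by design: "We will use a population PK approach using sparse sampling to study the PK effects of the two ACS regimens". In Table 1 the post-dose maternal PK samples are those at "1–4 hours post first dose", at 8–12 hours, at birth, and at 24–36 hours after the last dose. Fixed effects models specifies two compartments with first-order absorption, and Random effect models puts between-subject variability on all parameters where feasible.

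**The concern.** ANOVA needs one value per woman. With at most four post-dose samples and five structural parameters, a separate fit for each woman is not realistic. The individual PK parameters must in practice be empirical Bayes (post hoc) estimates from the population fit. Such estimates are pulled towards the mean of the model that produced them. When each drug has its own model, two things go wrong. The spread within each drug is too small, and the uncertainty of the two drug means is left out. Both make the ANOVA standard error too small.

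At stake is a set of between-drug statements on CL, V and ka, some of which could be called significant with no true difference behind them, in a study meant to inform dosing.

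**Working it through.** **Inputs from the document.** Sample size asks for 30 women with complete samples and allows for up to 40% loss: 30/(1 − 0.40) = 50 per arm per country, and 3 × 50 = 150 per country, as stated. Reading the 30 as per drug arm, two countries give 2 × 30 = 60 women per drug. The 5% level is taken from the planned 95% CIs. Shrinkage, variances and PK values are not given and are assumed below.

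**Formula.** Let a woman's own information on a log-parameter be y = μ + η + e, with var(η) = ω² and var(e) = s². Let B = ω²/(ω² + s²).

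- Individual estimate: m + B(y − m), where m is the drug's own mean.
- Variance of these estimates: B²(ω² + s²) = Bω². SD-shrinkage is thus 1 − √B, so B = (1 − shrinkage)².
- Variance of the drug mean that ANOVA assumes: Bω²/n.
- True variance of the drug mean: (ω² + s²)/n = ω²/(Bn).
- Ratio of ANOVA SE to true SE: √(B × B) = B.
- Actual error of a nominal 5% test: 2Φ(−1.96B).

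At shrinkage of 10%, 20%, 30% and 50%, B = 0.81, 0.64, 0.49 and 0.25. The error is then 11%, 21%, 34% and 62%.

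**Simulation of the formula.** This was a drug-by-country ANOVA (country is assumed as the second factor) with 30 women per cell and 4,000 runs:

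| B | Shrinkage | Formula | ANOVA, separate fits | ANOVA, one fit without drug term | Wald test on population estimates |
|---|---|---|---|---|---|
| 0.9 | 5% | 7.8% | 7.4% | 4.5% | 5.1% |
| 0.8 | 11% | 11.7% | 11.5% | 4.1% | 4.6% |
| 0.7 | 16% | 17.0% | 17.8% | 5.2% | 5.7% |
| 0.6 | 23% | 24.0% | 25.7% | 5.8% | 6.2% |
| 0.5 | 29% | 32.7% | 32.9% | 5.0% | 5.4% |
| 0.4 | 37% | 43.3% | 45.8% | 4.7% | 5.2% |

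In the single fit without a drug term the level holds, but both drugs shrink towards a common mean and the difference is multiplied by B. It is attenuated by 1 − 0.64 = 36% at 20% shrinkage and by 1 − 0.49 = 51% at 30%.

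**What shrinkage the Table 1 times might give.** A linearised one-compartment model was run with 60 women per drug, separate fits, known ω, a two-sample t-test on the drug effect, and 800 runs per scenario. Assumed values were half-life 5–9 h, ka 0.7–2/h, between-subject SD 0.3 for CL and V and 0.5 for ka, and residual SD 0.15–0.30. Each was run with and without the birth sample, giving 2 × 2 × 2 × 2 = 16 scenarios.

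| Parameter | Shrinkage | Actual error at nominal 5% |
|---|---|---|
| CL | 3%–12% | 5.6%–16.4% |
| V | 7%–23% | 8.5%–32.2% |
| ka | 24%–86% | 24.6%–96.6% |

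At 800 runs the Monte Carlo standard error near 5.6% is √(0.056 × 0.944/800) = 0.8 percentage points, so the best CL scenario cannot be told apart from 5%. The ka result fits the design, which has only one sample in the absorption phase of the first dose.

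**The case against.** The strongest reply is that the plan already contains a sound comparison. The same section compares population estimates by 95% CIs, and a Wald test on such estimates held 4.6%–6.2% in the simulation above. A stage-2 physiologically based model is also planned to compare the drugs' PK. This stands. A reader might infer that every between-drug conclusion depends on the ANOVA, but the document does not say so. What remains is that the word test is attached to the ANOVA, and nothing says which method governs if the two disagree.

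Several stronger readings are also unsupported:

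- **Several-fold inflation throughout.** The 34% and 62% figures need shrinkage of 30% and 50%, which the document does not give. Under the assumed values, several-fold inflation is clear only for ka.
- **Emax and EC50 fail as well.** They were not simulated. The article plans joint drug/PD models and does not say whether both drugs share one fit.
- **The 95% CIs will be judged by overlap, which would be too strict.** The article does not say how they will be compared.
- **The missing log scale is an error.** The article says only: "A log-normal parameter variability model or other appropriate parameter variability models will be considered for the PK and PD parameters". The scale of the ANOVA is a detail for the statistical analysis plan.

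Finally, the primary objectives in the Introduction are to describe each regimen's PK and PD and to compare PD with placebo. None is a test of one drug's parameters against the other's, and no power is attached to one. This lowers the weight of the point but does not remove it.

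**Conclusion.** The concern holds for the PK parameters. As written, with one PK model per drug, a two-way ANOVA on individual estimates understates the standard error by (1 − shrinkage)² and exceeds a nominal 5% level. Under the assumed PK values the excess ranges from slight to about three-fold for CL (6%–16%), from about two-fold to six-fold for V (9%–32%), and is at least about five-fold for ka (25% or more).

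The direction rests on two readings: that the individual parameters are post hoc estimates, a term the article does not use, and that the fits are separate by drug. The size rests on assumed PK values, a one-compartment approximation with known ω, and 60 women per drug. The planned two-compartment model has more parameters for the same samples and would not be expected to shrink less. It should be fixed before analysis, but it does not threaten a primary objective.

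**What to change.** State in the Statistical analysis section that between-drug inference is model-based. Either of two routes will do:

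- Report a 95% CI for the difference or ratio of the two drugs' population estimates, built from their standard errors. Different women receive each drug, so this needs little beyond the estimates already planned.
- Fit both drugs in one joint model with drug as a fixed effect on each typical parameter, test it by likelihood ratio, and report the ratio with its 95% CI.

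Keep the ANOVA and the individual estimates as descriptive, and report shrinkage for each parameter alongside them; it is not among the diagnostics named under Model performance diagnostics.

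The cost is some rewording and possibly one extra model run, with no change to sampling or data collection. Some differences that the ANOVA would call significant may no longer be so, ka most of all.

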### Study oversight

In addition to the monitoring procedures for the ACTION-III trial in accordance with the International Council for Harmonisation of Technical Requirements for Pharmaceuticals for Human Use (ICH) Harmonised Tripartite Guideline for GCP E6 (R2), additional monitoring activities will be conducted at all PK-PD study hospitals by independent trial monitors, the central laboratory team (Syngene International) and WHO TCU. Day-to-day oversight will be done by the principal investigators and co-investigators.

### Patient and public involvement

Patients were not directly involved in the design of this study.

## Discussion

ACS therapy remains inadequately optimised. The minimal therapeutically effective dose to enable fetal lung maturity and to minimise adverse effects has not been ascertained despite 50 years of being in clinical use. This study will describe the PK and PD of two different regimens of ACS that include either DEX or BET phosphate, given in the currently recommended and lower dose regimens, respectively.

Research involving non-human primates and sheep suggests that fetal plasma concentrations should be kept above 1 ng/mL for a duration of 48 hours to promote fetal lung maturation while avoiding excessively high plasma levels.^12^ Although this is an estimated threshold based on studies in sheep and primates, similar conclusions have also been drawn from clinical data.^31^ We are aware of only three previous human studies that evaluated the PK and PD of DEX and BET in reproductive age but non-pregnant women,^32^ PK of BET in vivo in pregnant women^31^ and PK of DEX and BET ex vivo using placental perfusion.^33^ While the first study done in non-pregnant adult women showed that the currently administered ACS doses result in short-term PD effects like increased glucose, suppressed cortisol, increased neutrophils and suppressed basophils, CD3CD4 and CD3CD8 lymphocytes in women, the latter two suggest that lower doses of ACS can achieve the suggested optimal drug levels required for desirable effects in the fetus. The current study will be the first to provide these data for two different regimens of ACS, both currently recommended for the early preterm period and a lower dose, in pregnant women in late preterm gestation, alongside information on maternal-fetal transfer of ACS with these regimens.

Only one study, the BETADOSE trial, has evaluated a lower dose of ACS in pregnant women on neonatal outcomes until. This non-inferiority trial compared full (12 mg plus 12 mg, 24 hours apart) versus half (12 mg single dose) dose of BETp and acetate and could not show that half dose was non-inferior to full dose. However, the choice of half dose in this trial was pragmatic, based on its effectiveness in achieving similar lung maturation as the full dose in sheep, and the halving of the total dose of steroids was achieved by front-loading the entire drug exposure. Hence, questions remain whether non-inferiority could be achieved by distributing a halved dose over the normal duration of a standard treatment, which would be more consistent with recent and historical data suggesting that a low-amplitude, extended duration of fetal steroid exposure is important to achieve fetal lung maturation. The ACTION-III trial incorporates a low dose regimen that is based on PK modelling, which could potentially achieve lung maturation at least as effectively as the dose currently recommended for use in the early preterm period, that is, 6 mg DEXAp regimen, but with possibly less disruption to the hypothalamic–pituitary–adrenal axis.^34^

Our study uses a popPK modelling approach that relies on concentration-time data from multiple individuals and allows the analysis of clinical data collected in a setting where rich data are not practical, as in the high-risk population of pregnant women at risk of preterm birth in the ACTION-III trial. While it uses technically complex mathematical and compartmental methods to reach conclusions, it allows an integration of the covariate information (eg, weight, race/ethnicity, renal/hepatic function, concomitant medications, etc). Therefore, information provided by the popPK model can help optimise ACS dose regimens in this population. However, we will not be able to assess the impact of genetic differences among women that could affect the PK or PD of antenatal steroids, or variations in placental metabolism that may influence cord blood levels.

To conclude, complications from preterm birth continue to be the leading cause of neonatal mortality, particularly in low-resource settings. ACSs are currently the only known effective intervention to enhance survival rates and reduce morbidity among newborns. However, our understanding of the PK and PD of this life-saving treatment is limited. This study aims to shed light on the PK and PD of ACS when used in real-world settings. The data generated will contribute to optimising ACS regimens and improve our understanding of important issues related to dosing strategies and the effects of the drugs at a biological level.

### Ethics and dissemination

The study has been approved by the WHO Ethics Review Committee ([name]; [contact]), ref: 0003488) on 3 March 2021 and the site-specific ethics committees of the participating leading institutions (India—Institutional Ethics Committee, Vardhman Mahavir Medical College and Safdarjung Hospital, Delhi (Ref No IEC/VMMC/SJH/Project 2023-11/392) and Institutional Ethics Committee, Translational Health Science and Technology Institute, Haryana (Ref No: THS 1.8.1/(170); India—Institutional Ethics Committee of KLE Academy of Higher Education and Research, Belagavi (Ref No: KAHER/EC/2023–24/D-19062302); Nigeria—University of Ibadan and University College Hospital Ethics committee, Ibadan (Ref No UI/EC/23/0429); Nigeria—Ethics and Research Committee, Obafemi Awolowo University Teaching Hospitals Complex, Ile-Ife (ERC/2023/11/17; dated 30/11/2023)). A written informed consent will be taken from all participants in line with ICH GCP guidance.

The results of the study will be published in a peer-reviewed journal and presented at scientific conferences.
